**Fig 4 pone.0319020.g004:**
[figure not shown]
Participant Flow Chart according to CONSORT guidelines (2010).

### Outcomes

The study outcomes are presented in Table 1, organized per the study’s research questions and Bowen’s framework [16] which evaluates different areas of intervention implementation that are directly relevant to our research aims.

**Table 1 pone.0319020.t001:** Cynnau|Ignite’s evaluation outcomes (organised by research question), methods and informants for evidence gathering.

	Dimension evaluated*	Outcomes	Informants		
			Learners	Stakeholders	Delivery Team
**Research Q1**	**Acceptability** How well is Cynnau|Ignite received?	Expected (positive and negative) outcomes of attending themes and overall participation in Cynnau|Ignite, for learners and their school/unit	PE	PE	PE
		Perceived (positive and negative) outcomes (and cost-benefit) of attending themes and overall participation in Ignite, for learners and their school/unit	PE	PE	PE
	**Integration** How well can Cynnau|Ignite be integrated into Cardiff University?	Perceived disruption(s) caused by Cynnau|Ignite	PE	PE	PE
	**Effectiveness** To what extent is Cynnau|Ignite successful in achieving its goals?	Perceptions about what in Ignite contributed to outcomes perceived and how	PE	PE	PE
		Perception about for who and under what circumstances does Ignite contribute (or not) to outcomes	PE	PE	PE
	**Impact** The short- and longer-term effects or influence of Cynnau|Ignite	Perceptions about long-term impact(s) of staff attending Ignite (e.g., career development) at personal, school, and Institutional level	PE	PE	PE
		Perceived impact from and plans to continue/extend Action Learning projects (e.g., other contexts, further developments, networks, etc.)	PE	PE	PE
**Research Q2**	**Demand** To what extent is Cynnau|Ignite likely to be used?	Number of brochures requested	DM		
		Number of EoI submitted	DM		
		Final number of participants & per/school	DM		
		Background and professional profile of applicants	PE		
		Perceptions of demand	PE	PE	PE
		Attendance rate	DM		
		Attendance rate for optional Action Learning module (R)	DM		
		Contributors and learners’ engagement during sessions	OBS		
	**Acceptability** How well Cynnau|Ignite is received? Is it suitable and appropriate to meet the needs of participants, stakeholders and the delivery team?	General views of and feedback about Cynnau|Ignite	PE	PE	
		Perceptions of most and least useful elements or sessions of Ignite	PE		PE
		For each Stream: multiple Likert-type questions assessing acceptability of content and delivery, plus one open-ended question for additional feedback	SE		
		Observation of and feedback/comments from participants re acceptability during sessions	OBS		
**Research Q3**	**Implementation** To what extent can Cynnau|Ignite be delivered as planned?	Perceptions of barriers and facilitators of programme implementation			PE
		Description of changes to planned implementation and rational			PE
		Description of changes to planned implementation and rational			DM
		Description of changes happening during sessions and rational	OBS		
	**Practicality** Can Cynnau|Ignite be carried out as planned with the resources available?	Perceptions of barriers and facilitators of attendance	PE	PE	PE
		Perceptions of barriers and facilitators of implementing Action Learning projects	PE	PE	PE
		Perceptions of barriers and facilitators of general enactment of Cynnau|Ignite learning, skills, and values	PE	PE	PE
		Observation of and feedback/comments from participants re practicality during sessions	OBS		
	**Adaptation** How well can we expect Cynnau|Ignite to perform at other HEIs or staff career development levels?	Perceived challenges of implementing Ignite at other HEIs or staff career development levels	PE		PE
		Perceived changes needed to implement Ignite at other HEIs or staff career development levels	PE	PE	PE
	**Integration** How well can Cynnau|Ignite be integrated into Cardiff University?	Perceived organizational fit of Cynnau|Ignite (resources, culture, practicalities…)	PE	PE	PE
		Perceptions of sustainability of implementing Cynnau|Ignite	PE	PE	PE
		Observation of and feedback/comments from participants re fit of Ignite with organizational environment/procedures during sessions	OBS		
**Research Q4**	**Effectiveness** To what extent is Cynnau|Ignite successful in achieving its goals?	Analyses on TPB outcomes (intentions, attitudes, norms, perceived behaviour control) measured at T1 and T2.	QE		
		Differences in TPB outcomes (intentions, attitudes, norms, perceived behaviour control) for R-only learners, measured at T2 and T3	QE		
	**Impact** The short- and longer-term effects or influence of Cynnau|Ignite	Differences in perceptions of PRC at Cardiff University, as measured in the Research Culture Survey, between all Ignite learners and a matched group of CU staff who did not participate in Ignite, and between learners and control group.	QE		
		Nr of Action Learning projects implemented and impact narratives from projects	DM		
		Differences in uptake of mandatory training between learners and control group	DM		
		Institutional decision about funding Ignite longer-term		DM	

Legend. DM =  data monitoring via University/Ignite procedures, OBS =  semi-structured behavioural observations during Cynnau|Ignite sessions, QE =  Quantitative evaluation conducted via online survey, PE =  Process evaluation, based on individual semi-structured interviews or focus groups.

## Materials and methods

### Study setting

Cynnau|Ignite will be fully implemented at Cardiff University. The university is part of the Russell Group, comprised of 24 research-intensive institutions in the UK, and 90% of its research was classified as internationally excellent.

### Participants

The intervention group will consist of all learners, comprised of four cohorts (two T&R cohorts, one R and one PST/S cohort) with 32 learners in each. All those accepted into Cynnau|Ignite will be eligible to take part in the study and will integrate the intervention trainee groups. Selection criteria for Cynnau|Ignite will be those employed at Cardiff University at grade six, seven or eight as Teaching and Research, and Research-only staff, along with Professional Service staff, or Technicians at grades 5 to 8, in any discipline. Applicants will be expected to demonstrate that they have an interest in PRC and are available to attend all sessions, with allowances made for those who are unable to attend a single session. These criteria mirror common practice for similar training programmes at Cardiff University and will be likely to remain unchanged, unless if demand will need to be addressed in future Cynnau|Ignite iterations. We expect high participation and low attrition in the intervention group. No concealment or blinding will be used in this research. All learners will be allocated to either the Teaching and Research, Research-Only, or Professional Services, Technicians and Specialists version depending on their career path.

Inclusion criteria for the control group will be being a Cardiff University employee at grade six, seven, or eight who is not enrolled in the programme. Based on moderate attrition rates between 20–50% [17,18] observed in repeated measures surveys and organizational research, we intend to recruit a total of 96 staff members for this group, with a maximum of 32 participants each from T&R, R and PST/S roles. A power analysis conducted using GPower [19] indicates that this will provide enough power to detect small to moderate effect sizes (repeated measures ANOVA, p = .90, f =  0.15, α = .05) in differences between the learner and control groups in changes in intentions from baseline (T1) to follow up (T2) and in differences between the R and control groups in changes in intentions from baseline (T1) to follow ups (T2 & T3).

To assess the acceptability of Cynnau|Ignite, and its feasibility for use at Cardiff University as a tool to promote positive research culture and leadership development, we will invite five members from each of the intervention groups, as well as Heads of School and Directors of Research, and members of the delivery team to participate in the process evaluation via semi-structured interviews or focus groups. This sample size was deemed appropriate to support the in-depth exploratory qualitative analysis required while capturing data from all necessary groups involved in this research through purposeful sampling.

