The programme will primarily be delivered face-to-face, however online access will be provided if it is requested as a reasonable adjustment due to personal circumstances (considered on a case-by-case basis). All training sessions will be held in conference rooms, either within Cardiff University or at an external venue, and rooms will be large enough to accommodate 32 participants and several members of the delivery team. Each session will run from 9 am until 4.30 pm, inclusive of lunch and rest breaks, and all learners must commit to attend all modules during the application process, with some flexibility given for those who cannot attend a single date. Attendance will be monitored and recorded.

Throughout, learners will have access to a physical Cynnau|Ignite workbook, featuring materials which guide them through all individual and group activities for each module (e.g., values and self-leadership assessments), and an online Microsoft Teams channel, where learners will have on-demand access to PowerPoint slides summarizing each module, and related reading materials. Using this channel, learners will have the ability to interact with programme facilitators and others in their cohort and share PRC resources. Learners are not restricted from engaging in other PRC initiatives or training programmes on their own volition, both within and outside Cardiff University.

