### Recruitment

The Cynnau|Ignite programme brochure will inform staff they will be invited to participate in this evaluation study. Staff who apply and are selected for the programme will receive an invitation to participate in the research in their Welcome Pack. In the event Cynnau|Ignite exceeds recruitment targets eligible participants will be chosen to maximise representation across roles, schools and units, however if this is not possible, participants will be randomly selected. As such, recruitment for the Cynnau|Ignite participant group will begin on 1^st^ September 2024, and end 8^th^ January 2025 (dependant on cohort start date). Recruitment for the control group will begin 1^st^ September 2024 and run until 1^st^ July 2025 or until target numbers have been reached and will first target staff who indicates an interest in attending Cynnau|Ignite (e.g., request brochure) but do not apply or are not selected, via email invitation. If recruitment targets are not reached with this strategy, participants will be recruited more widely within the university using CU communication channels. All non-trainee participants (e.g., heads of schools) will be invited to participate via email.

All prospective participants will be signposted to the Participant Information Sheet and Consent Form, where they will be required to provide full written informed consent before taking part in this research. After providing consent, participants will be directed to the baseline survey.

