Effectiveness and impact (Research Question 4) will be reported for all learners, but the analytical strategy will depend on the final sample achieved. Cardiff University has a total of 26 academic schools, all of which are eligible for Cynnau|Ignite. To account for non-independence of data we will use multi-level modelling [30] with learners (level 1) nested within schools (level 2), but only if the recommended 20 schools/units are achieved [31]. If this is not possible, we will use two-way Mixed ANOVA. Analysis will investigate how Cynnau|Ignite affects self-reported intentions and actual PRC behaviours (primary outcomes), attitudes, norms and PBC (secondary outcomes), with Group (Cynnau|Ignite, Control) as the between-subject variable and Time (T1, T2) as the within-subject factor. Similar analysis will be used to compare each Cynnau|Ignite group (T&R, R, PST/S) with the control group and to investigate changes in the study outcomes across a 6-month period following Cynnau|Ignite, the latter with Time (T2, T3) as the within subject factor for the R-only cohort. Statistical significance will be indicated if *p* < 0.05 and effect sizes will be reported for all analysis. Finally, we will quantitatively analyse the organisational impact of Cynnau|Ignite by investigating learner and control group differences with multilevel modelling, or Mixed ANOVA if the necessary units are not reached, in perceptions of PRC at Cardiff University. Descriptive and inferential statistics will be used to map the impact of Cynnau|Ignite on impact indicators, such as the implementation of Action Learning projects related to research culture, and learners’ uptake of mandatory staff training compared to those who did not participate in Cynnau|Ignite.

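### Controls recruited through the wider call need show no interest in positive research culture, so change tied to motivation can enter the primary Group-by-Time comparison

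*Protocol article*

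**What the plan says.** **Learners.** Participants sets the entry condition: "Applicants will be expected to demonstrate that they have an interest in PRC and are available to attend all sessions". The programme description adds that "all learners must commit to attend all modules during the application process", with some leeway for one missed date. Four cohorts of 32 are planned.

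**Controls.** Participants asks only that a control be "a Cardiff University employee at grade six, seven, or eight who is not enrolled in the programme". The target is 96, with at most 32 from each of the three role groups. Recruitment works in two steps. The campaign "will first target staff who indicates an interest in attending Cynnau|Ignite (e.g., request brochure) but do not apply or are not selected"; then, "If recruitment targets are not reached with this strategy, participants will be recruited more widely within the university using CU communication channels". Neither the inclusion criteria nor the second step carries a condition on interest, availability or commitment.

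**Analysis.** Analytical methods tests self-reported intentions and behaviours as primary outcomes, "with Group (Cynnau|Ignite, Control) as the between-subject variable and Time (T1, T2) as the within-subject factor". Controls from both steps therefore sit in the same level of Group.

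**Limitations.** The Discussion concedes that controls cannot be matched on career pathway and that programme effects will be hard to separate from wider change in the sector. It does not mention self-selection on interest.

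**The concern.** Interest in PRC is close to the outcome. The Introduction adopts the Theory of Planned Behaviour, under which favourable attitudes strengthen intentions, and intention is a primary outcome. Learners are thus selected on a precursor of the outcome, while fallback controls are not.

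Group-by-Time removes a baseline difference that stays constant. It does not remove a difference in how the groups would have changed without the programme. Two routes are plausible and pull in opposite directions. Motivated staff may increase their PRC intentions and behaviours on their own initiative, which would look like a programme effect. Staff who applied at a temporary peak of enthusiasm may fall back, which would hide one. At stake is how cleanly the primary result can be attributed to the programme.

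**Working it through.** **1. The plan's own figure.** Participants states power 0.90 at f = 0.15, alpha 0.05. With noncentrality λ = f²·N·m/(1 − ρ), two groups, m = 3 times and an assumed ρ of 0.5 (the correlation is not stated), N = 96 gives λ = 0.0225 × 96 × 3 / 0.5 = 12.96 and power 0.902. So 96 reproduces the stated power as a total N. For the main two-time contrast, 128 learners against 77 controls (96 less the lower attrition figure of 20%) gives power 0.985. Size is not the problem, and power does not protect against bias.

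**2. Scale of the target effect.** With two groups and two times, f = δ/4, where δ is the difference in mean change in SD units. Hence f = 0.15 means δ = 4 × 0.15 = 0.6 SD. A differential of 0.2 SD is one third of that.

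**3. False-positive rate with no programme effect.** Let δ be the difference in change between learners and general staff that would arise anyway.

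- SE = √[2(1 − ρ)(1/n₁ + 1/n₂)] = √[2 × 0.5 × (1/128 + 1/77)] = 0.144
- Rejection probability = Φ(−1.96 + δ/SE) + Φ(−1.96 − δ/SE)
- For δ = 0.2: δ/SE = 1.387, so Φ(−0.573) + Φ(−3.347) ≈ 0.284

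If a share w of controls comes from the wider call, and first-step controls change as learners would have done without the programme, the bias is w·δ.

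| δ (assumed, SD) | all controls from wider call | half | none |
|---|---|---|---|
| 0.1 | 11% | 6% | 5% |
| 0.2 | 28% | 11% | 5% |
| 0.3 | 55% | 18% | 5% |

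For δ = 0.2 with all controls from the wider call, the rate is 22% at ρ = 0.3 and 43% at ρ = 0.7. At ρ = 0.5 it is 32% with all 96 controls retained and 22% with 48 (50% attrition).

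**4. The opposite direction.** A decline of 0.2 SD in learners, unrelated to the programme, would turn a true 0.6 SD into 0.6 − 0.2 = 0.4 SD on average. For decline from a peak, suppose that entry on interest lifts learners' T1 mean by 0.5 SD. Regression to the mean is then at most (1 − r) × 0.5: 0.25 SD at r = 0.5 and 0.10 SD at r = 0.8. This is an upper bound, because it treats selection as acting on the T1 score itself. Entry in fact depends on interest shown at application. If that interest is stable, or r is below 1 only through measurement error, the drift is zero.

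**The case against.** The strongest reply is that the plan already has the natural defence: control recruitment starts with people who showed interest, including unselected applicants, and the wider call opens only if targets are missed. That stands. A reader might infer that the study compares an enriched group with general staff in any event; the documents do not support this. The wider pool is also still limited to grades 6 to 8 and 32 per role. First-step controls are not a perfect match, however: those who asked for a brochure and did not apply chose differently from applicants.

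Secondly, covariates and sensitivity analyses are commonly left to an analysis plan, and none is shown. Their absence here is no fault in itself. But the recruitment rules and the data to be collected are fixed in the protocol, and no later analysis can use an interest measure or a source that was not recorded. The baseline survey does collect attitudes and intentions from everyone, so part of the difference could be examined as things stand. Those variables are themselves study outcomes, though, and do not show how a control was recruited.

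Thirdly, the authors disclose weak control of bias and unmatched controls. This is fair, but it does not name this mechanism.

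Two further readings are tempting and fail:

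- **Ceiling.** Learners who start high on a bounded scale have less room to rise. That compresses their rise whoever the controls are, and controls with no shift change by zero at any baseline. It is no reason to screen controls.
- **Contradiction.** The Study design section describes selection of learners as slight. That is relative wording about a pragmatic design, and showing interest and availability is a light criterion. The two statements can coexist.

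**Conclusion.** The concern holds in a conditional form. Learners are selected on interest, fallback controls are not, and both control sources enter the primary contrast together. To the extent that the fallback is used, change related to motivation can be mistaken for a programme effect or mask one.

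Direction and size are unknown. The 28% and 11% rest on an assumed differential of 0.2 SD, ρ = 0.5, 20% loss among controls only, and first-step controls who would change as learners do; the documents give neither the differential nor the correlation. If no control comes from the wider call, the rate is the nominal 5% under the same assumptions.

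A reader might go further and say that no result could be attributed to the programme. The documents do not support that: the first recruitment step offers partial matching on interest, and the share of fallback controls is not yet known. The supported conclusion is that attribution would be less clean than the plan implies, and that a small addition to data collection would help.

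**What to change.** - **Recruitment and Materials:** record each control's source (unselected applicant, brochure requester, wider call). Add one baseline item, asked of both groups, on interest in PRC and willingness to attend such a programme.
- **Analytical methods:** keep all controls in the primary analysis and adjust for baseline interest. The adjustment must include an interest-by-Time term, since a main effect alone does not address differential change. Prespecify a sensitivity comparison restricted to controls who applied or expressed interest.
- **Discussion:** name self-selection on interest as a limitation, and report how many controls came by each route.

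The cost is one survey item, one source flag and one further analysis. The restricted comparison will be less precise. Stated willingness is also hypothetical and weaker than applying and committing to full-day sessions, so the adjustment will reduce the problem without removing it. Keeping all controls in the primary analysis avoids giving up sample that the fallback exists to supply.

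### Professional services and technical staff may join the programme from grade 5, but controls must be grade 6 to 8, so any grade-5 learners have no same-grade controls

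*Protocol article*

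**What the plan says.** All the eligibility rules stand in the Participants section of the protocol article.

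- Academic learners: "those employed at Cardiff University at grade six, seven or eight as Teaching and Research, and Research-only staff".
- Other learners: "along with Professional Service staff, or Technicians at grades 5 to 8, in any discipline".
- Who is analysed as a learner: "All those accepted into Cynnau|Ignite will be eligible to take part in the study and will integrate the intervention trainee groups". Grade-5 entrants are therefore in the intervention group.
- Learner numbers: "four cohorts (two T&R cohorts, one R and one PST/S cohort) with 32 learners in each".
- Controls: "Inclusion criteria for the control group will be being a Cardiff University employee at grade six, seven, or eight", with the further condition of not being enrolled. There is no exception by role.
- Control numbers: "we intend to recruit a total of 96 staff members for this group, with a maximum of 32 participants each from T&R, R and PST/S". The control group is thus meant to include PST/S staff.

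Under Analytical methods, the main analysis is Group (learners, controls) by Time (T1, T2). Each learner group, PST/S included, is then compared with the control group in a similar way. The article does not say that grade-5 learners are left out of either comparison. The Discussion concedes that controls cannot be matched on career pathway; it does not mention grade.

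**The concern.** The comparison is not randomised, so comparability depends heavily on who is allowed into each group. Here one eligible learner grade is shut out of the control group by rule, not by the accidents of recruitment. A grade term in a model could only extrapolate at grade 5, because no control is observed there.

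Grade plausibly bears on autonomy and access to resources. The Introduction describes perceived behavioural control in terms of having the skills and resources to act. The link to grade is an inference; the article does not make it.

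The rule also works against the recruitment plan. The Recruitment section turns first to staff who showed interest but did not apply or were not selected. Grade-5 staff in that pool are close counterparts of grade-5 learners, and the control criterion rejects them.

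**Working it through.** The plan gives no figure on this point to reproduce. The check sets the rules side by side and then sizes the possible effect.

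**1. Overlap of eligible grades**

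| Role | Learners | Controls | Grade without controls |
|---|---|---|---|
| T&R, R | 6, 7, 8 | 6, 7, 8 | none |
| PST/S | 5, 6, 7, 8 | 6, 7, 8 | 5 |

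**2. How many learners could be affected.** Learners: 4 × 32 = 128, of whom 32 are PST/S. The number at grade 5 is not stated. It lies between 0 and 32, that is 0 to 100% of the PST/S cohort and 0 to 25% of all learners.

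**3. Size of bias in the T1-T2 analyses.** Let q be the fraction of PST/S learners at grade 5, and d the difference, in SD units, between the change grade-5 staff would show without the programme and the change shown by grade 6-8 staff. A constant grade difference in level cancels in the Group by Time term, so only d matters.

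- PST/S versus control: bias = q × d
- All learners versus control: bias = q × d × 32/128 = q × d / 4

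Neither input is in the article. Assumed ranges are q = 0.25 to 0.5 and d = 0.2 to 0.3.

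- PST/S: 0.25 × 0.2 = 0.05 to 0.5 × 0.3 = 0.15 SD
- Pooled: 0.05/4 = 0.0125 to 0.15/4 = 0.0375 SD, about 0.01 to 0.04 SD

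If q = 0 or d = 0, the bias is zero.

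**4. Against sampling error.** With a pre-post correlation of 0.5 (assumed), the SD of change is √(2 × (1 − 0.5)) = 1 SD. For 32 PST/S learners, the standard error of the difference in change is √(1/32 + 1/96) = 0.20 with all 96 controls and √(1/32 + 1/48) = 0.23 after 50% control attrition. The upper assumed bias of 0.15 is below one standard error.

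**5. Against the planned effect.** The sample-size statement reads "repeated measures ANOVA, p = .90, f = 0.15, α = .05". The conventional two-group conversion gives 2f = 0.30 SD. If f is instead the interaction effect in a 2 × 2 design, the difference in change is 4f = 0.60 SD. The article does not say which applies. The pooled bias is 0.0125/0.30 = 4% to 0.0375/0.30 = 13% of the first figure, or 2% to 6% of the second. The PST/S bias is 17% to 50% of the first, or 8% to 25% of the second.

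**6. Power.** For the interaction test with f = 0.15, two-sided α = 0.05, correlation 0.5 and noncentrality N f² × 2/(1 − ρ), scaled by 4n₁n₂/N² for unequal groups, power with 128 learners is 0.94 with 48 controls and 0.99 with 96. Removing all 32 PST/S learners takes the 48-control figure only to 0.92. The mismatch is one of comparability, not of power.

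**The case against.** The strongest reply is that the consequence may be nil. Nothing shows that any grade-5 staff will enrol. The analysis is of change, so stable grade differences in autonomy or perceived control drop out, and the article gives no reason to expect grade-dependent change over about six months. Perceived behavioural control is also only a secondary outcome. All of this stands, and it is why the point is minor.

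It also stands that the comparison with the larger possible bias is already weak. The PST/S cohort is compared with a control group that may be two-thirds T&R and R staff, and the stated power covers all learners and the R cohort, not PST/S. The Discussion admits an unmatched control group, and the Study design section accepts low bias control. A common grade rule would leave that larger mismatch in place.

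This does not dispose of the point. The admitted limitation concerns career pathway and is put down to recruitment timing and uncertain quotas. Excluding one grade by rule is a separate and avoidable matter. The matched group in Table 1 belongs to the Research Culture Survey comparison and is listed apart from the control group, so it does not fill the gap. Nor is this a detail left to a fuller document: both criteria are stated, and they differ.

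A reader might infer that the whole PST/S cohort, a quarter of all learners, is confounded by grade, or that grade-5 learners have no comparable controls at all. The article supports neither. Only learners actually at grade 5 are affected, and PST/S staff at grade 6 and above remain eligible as controls.

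**Conclusion.** The two eligibility rules do not match, and this is certain from the text: any grade-5 learners have no same-grade controls. Whether bias follows is not known. In the T1-T2 analyses it requires both that grade-5 staff enrol and that they would have changed differently without the programme. Under the assumed inputs it is 0.05 to 0.15 SD in the PST/S comparison and about 0.01 to 0.04 SD in the pooled one. It would be wrong to conclude that the pooled result is invalid.

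The learner-control comparison of mandatory training uptake is not described as a change from baseline, so a stable grade difference could enter there; the article gives nothing from which to size it.

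This is a low-priority correction, worth making because it is avoidable and nearly free.

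**What to change.** Set control eligibility equal to programme eligibility by role: grades 6-8 for T&R and R, grades 5-8 for professional services staff and technicians. Keep the total of 96 and the cap of 32 per role. The cost is one line in the criteria and a minor ethics amendment, with no extra recruits.

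The Recruitment section ends control recruitment by 1 July 2025 at the latest. If it has closed, add a sensitivity analysis of the PST/S and pooled effects restricted to grade 6-8 learners, and report how many learners were grade 5. The programme must know learners' grades to apply its own selection criteria, so the cost is one extra analysis.

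The pooled restriction costs little precision. The PST/S restriction costs more: if half the cohort is grade 5, 16 learners remain and the standard error rises from 0.20-0.23 to √(1/16 + 1/96) = 0.27 with 96 controls or √(1/16 + 1/48) = 0.29 with 48 (correlation 0.5 assumed). It should be read as a check on the direction and rough size of the effect.

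Neither change addresses the lack of career-pathway matching, which should stay among the stated limitations.

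### The label small to moderate does not fit f = 0.15 for a Group-by-Time interaction: the main contrast detects about 0.44 to 0.55 SD at 90% power, and the R-versus-control contrast only 0.67 to 0.75 SD (correlation of .5 assumed)

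*Protocol article*

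**What the plan says.** The sample-size justification is in the Participants section of the protocol article. It plans "four cohorts (two T&R cohorts, one R and one PST/S cohort) with 32 learners in each", which is 128 learners, and 96 controls with an anticipated loss of 20 to 50%. It then cites a G*Power calculation and concludes that "this will provide enough power to detect small to moderate effect sizes", with these settings: "small to moderate effect sizes (repeated measures ANOVA, p = .90, f = 0.15, α = .05".

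The claim covers two contrasts:
- "differences between the learner and control groups in changes in intentions from baseline (T1) to follow up (T2"
- "differences between the R and control groups in changes in intentions from baseline (T1) to follow ups (T2 & T3"

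Both are Group-by-Time interactions. Analytical methods confirms the 2x2 layout of the main one: "with Group (Cynnau|Ignite, Control) as the between-subject variable and Time (T1, T2) as the within-subject factor". The statement does not express f as a difference in change, and gives neither the assumed correlation between time points nor the G*Power effect-size option.

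**The concern.** The usual labels for f (0.10 small, 0.25 medium) rest on a comparison of two group means, where f = d/2. On that scale f = 0.15 is d = 0.30, and *small to moderate* is a fair description. In a 2x2 interaction the same f stands for a difference in change twice as large, so the label does not carry over.

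This is the only sample-size justification in the article, and it concerns intentions, a primary outcome. A reader who trusts the label would expect a true difference in change of about 0.3 SD to be found nine times in ten. Such a reader could take a non-significant result as evidence against effects of that size.

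**Working it through.** **Inputs.** From Participants: f = 0.15, alpha .05, power .90 (printed as "repeated measures ANOVA, p = .90"), 128 learners of whom 32 are R, and 96 controls. Control loss of 20% or 50% leaves 77 or 48. Learner loss is described as low and is taken as zero. Assumption: the correlation ρ between time points is .5, with a range of .3 to .7. Clustering by school is ignored.

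**Step 1: reproduce the stated power.** In G*Power's default within-between interaction test, λ = f²·N·m/(1−ρ), df1 = (k−1)(m−1) and df2 = (N−k)(m−1), with k groups and m times.
- 2x2, ρ = .5: λ = 0.0225 × 2N/0.5 = 0.09N. N = 120 gives λ = 10.8 and power 0.903. The planned N = 224 gives 0.994, and N = 176 (50% control loss) gives 0.977. At ρ = .3 these two become 0.965 and 0.917.
- 2x3, ρ = .5: λ = 0.135N. N = 96 gives power 0.902. For R versus control, N = 128 gives 0.967, N = 109 gives 0.937 and N = 80 (50% control loss) gives 0.838.

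So the figure of .90 at f = 0.15 reproduces under the default option.

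**Step 2: turn f into a difference in change.** Let D be the difference in change. Take cell means 0 and D for learners, and 0 and 0 for controls. The interaction effect in the learner T2 cell is D − D/2 − D/2 + D/4 = D/4, and every cell has ±D/4. Hence f = D/(4·SD), and f = 0.15 gives D = 4 × 0.15 = 0.60 SD whatever ρ is. With unequal groups it is 0.61 SD (128:96) or 0.67 SD (128:48). Cross-check: the SD of change is SD·√(2(1−ρ)), which equals SD at ρ = .5. A two-sample t test on change with 60 per group and d = 0.60 has power 0.903, the same as Step 1.

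**Step 3: the other reading of f.** Under the partial-eta-squared convention f = d/2, so f = 0.15 is d = 0.30 on the change score, which is 0.30 SD at ρ = .5. Then 90% power needs 469 to 471 people. The design has 128 + 96 = 224, which gives 0.61 under G*Power's Cohen option.

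**Step 4: what the planned sample detects.** Noncentral t on T1-to-T2 change scores, two-sided .05:

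| Comparison | Detectable at 90% power, SD: ρ = .5 (ρ = .7 to .3) | Power at 0.30 SD: ρ = .5 (ρ = .3 to .7) |
|---|---|---|
| 128 v 96 | 0.440 (0.341 to 0.521) | 0.600 (0.464 to 0.815) |
| 128 v 77 | 0.470 (0.364 to 0.556) | 0.544 (0.417 to 0.762) |
| 128 v 48 | 0.552 (0.428 to 0.653) | 0.422 (0.319 to 0.624) |
| R: 32 v 96 | 0.667 (0.517 to 0.789) | 0.308 (0.234 to 0.469) |
| R: 32 v 77 | 0.688 (0.533 to 0.815) | 0.293 (0.223 to 0.446) |
| R: 32 v 48 | 0.750 (0.581 to 0.887) | 0.255 (0.195 to 0.388) |

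At 0.50 SD and ρ = .5 the main contrast has power 0.958, 0.932 and 0.836 in the same order of control loss.

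**Step 5: correlation needed for 90% power at 0.30 SD.** For learners versus control, ρ must be about .77 with no loss, .80 with 20% control loss and .85 with 50%. For R versus control it must be about .90 or higher.

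**The case against.** The stated number is met. At f = 0.15 the main contrast has power above .90 for every ρ from .3 to .7, even with half the controls lost. Because the sample exceeds the 120 needed, its detectable effect is not 0.60 SD. It is 0.44 SD, or 0.47 SD with 20% control loss, and both lie between the conventional small (0.2) and medium (0.5) marks. All of this stands. A reader might infer that the study is not powered for the effect it states, or that no small-to-moderate effect is within its reach. The document does not support either inference.

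The results also depend on a correlation that the article does not give and that the full protocol may. That is fair, and the omission alone is no fault in a condensed article. But the conversion to 0.60 SD does not depend on ρ, and no ρ between .3 and .7 gives 90% power at 0.30 SD.

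The R-versus-control rows use T1 and T2 only, whereas the power statement names three time points. This too is fair, and the 2x3 figures in Step 1 are kept separate for that reason. However, Study design has the controls complete baseline and short-term follow-up only, so T1 to T2 is the change that both groups supply.

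Finally, the article does not say that a null result would exclude small effects, and it promises effect sizes for every analysis. The misreading is a risk created by the label, not a stated plan.

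**Conclusion.** The concern holds as a mislabelled effect size. Under the default option, f = 0.15 is a 0.60 SD difference in change and the label is wrong. Under the other convention the label fits, but the sample is less than half of what is needed (224 against about 470).

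For learners versus control, the planned sample covers the moderate end of the promised range if control loss is low, but not the small end, where power at 0.30 SD is well short of .90. For R versus control the label fails most clearly: the detectable difference is above medium at every attrition level for ρ of .3 to .7, and the 2x3 power at f = 0.15 drops to 0.84 when half the controls are lost (ρ = .5).

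These sizes assume equal variances at both times, no learner loss and no clustering.

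**What to change.** In Participants, replace the phrase *small to moderate effect sizes* with the difference in change, in SD units, detectable at 90% power. Give it for each contrast separately after 0 to 50% control attrition, and name the correlation and G*Power effect-size option actually used. If the correlation was .5 with the default option, the text could read:

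*With 128 learners and 96 to 48 controls retained, the study has 90% power for a difference in T1-to-T2 change of 0.44 to 0.55 SD. For the R cohort (32) versus control the corresponding range is 0.67 to 0.75 SD. Differences near 0.3 SD are not covered at 90% power unless the correlation between time points is high (about .8 for all learners versus control).*

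If another correlation was used, recompute the figures with it. If the three-time-point claim for R versus control is kept, report its power after attrition separately. The cost is wording only: sample size and analysis are unchanged, but the stated figure becomes less favourable.
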